### Informed consent

On meeting, all of the inclusion criteria in the clinical examination, Participants will be informed about the purpose of the study and the examination and treatment procedures involved in this project and a written informed consent will be obtained from all participants who agree to take part in this study, before data collection. Participants will have the right to refuse core training treatment and withdraw from the study at any time without penalty. The same physiotherapist who is administering the intervention will obtain it.

### Examiner

Participants will be evaluated by a physical therapist who is a PhD candidate with more than 10 years of clinical experience (RB), the same physiotherapist collect the pre-treatment and post-treatment data from each participant and also will provide core stabilization program.

### Equipment

#### Three dimensional motion analyses

A three dimensional approach will be used to kinematic analysis of trunk, lumbar and pelvis pre/post treatment in all participants. Six cameras with the resolution of 1.3 megapixel (Qualisys, Gothenburg, Sweden) will be set up for measure kinematics of the trunk, lumbar and pelvis during gait. Gait kinematic variables will be captured at 100 Hz using a 10MX T20 camera three dimensional motion capture system (Qualisys, Gothenburg, Sweden) and will be analyzed using QTM software (Qualisys, Sweden), MATLAB version R2015 and Microsoft Excel version 2015 (Microsoft, Reading). Using palpation, anatomical landmarks will be identified by physical therapist for each subject and 13 reflective markers with the size of 10 × 8 mm and circular cross-section will be placed on the landmarks to capture kinematics of each segment with the movement analysis system. While the participant are in a flexed standing position supporting themselves upon a stool, marker locations will be confirmed by counting of the spinous processes from T_12_ down to the S_2_ spinous process [3]. The standardized marker location is chosen based on rationales including higher repeatability and maximize visibility as suggested by Seay et al. [18, 47] and Hidalgo et al. [48]. Trunk, lumbar and pelvis segments are defined according to the following to measure trunk and lumbar motion relative to the pelvis:

Trunk segment: is defined by markers on the acromion processes and spinous process of T12 withmotion measured as the relative angle between the trunk and pelvic segments [18, 47].

Lumbar segment: is defined by markers on the spinous process of T12 and two paraspinal markers over the angles of the ribs lateral to T12 (where the transverse process of T12 joins with the rib), with motion measured as the relative angle between the lumbar and pelvic segments [49]. Although, the potential limitations of using paraspinal markers vs. rigid clusters (e.g., soft tissue artefact), this model has been demonstrated high repeatable for detecting lumbar segment movements in CLBP [49, 50]. Kiernan et al. [51] compared two kinematics protocols for quantifying lumbar movement including rigid cluster and skin markers. They reported that rigid clusters might be more susceptible to wobble error relative to the skin markers. Therefore greater levels of variability recorded by the rigid cluster during lumbar rotation suggests the skin surface markers may be more suited to studies where axial rotation is a consideration such as gait studies [51].

Pelvis segment: is modelled by placing 4 markers on the anterior superior iliac spine (ASIS) and posterior superior iliac spine (PSIS) in both sides based on previous studies [48, 52].

In order to detect gait cycle during gait trials 4 markers will be placed on posterior calcaneal tubercle (posterior heel center) and on 5th metatarsophalangeal joint (MTP) of both feet [43].

Data will be recorded for 3 gait trials in both with and without load in pre- and post-intervention. After a static trial, participants will be asked to walk barefoot from one end of a marked walkway to the other that is 10 m in length at their self-selected comfortable walking speed.

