**Discussions:**

We will quantify the effectiveness of CSTP on the kinematic of trunk, lumbar and pelvis during gait. Comparing the kinematic pattern and movement variability using CV_o_ and CV_p_ can contribute to better understand the motor control strategy and movement pattern of the spine during an anterior load carriage task between patients with NCLBP and healthy.

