It is possible that the trunk stiffness, and altered lumbar and trunk kinematics including higher movement variability and lower displacement are a manifestation of commonly associated core muscles dysfunction [9]. Core muscles dysfunction can contribute to the poor motor control during gait that may result in compensatory trunk stiffness [19]. To the best of authors’ knowledge, the effect of isolated core training program on the between-trial variability and displacement of the trunk has not been investigated yet. On the other hand, the effect of an anterior load carriage task that is disruptive for LPS to alter the trunk movement pattern has not evaluated in previous studies. Thereby, previous studies have failed to reveal the effect of specific core training program on the lumbar, and trunk kinematics including between-trial variability as well as peak displacement during gait including anterior load carriage.

The study hypotheses are as follows:NCLBP group shows a lower between-trial variability and peak displacement of the trunk movement relative to the pelvis in the sagittal, frontal and transverse planes during gait with and without load compared to healthy.NCLBP group shows a lower between-trial variability and peak displacement of the lumbar movement relative to the pelvis in the sagittal, frontal and transverse planes during gait with and without load compared to healthy.Core stabilization exercise therapy increases the between-trial variability and peak displacement of the trunk relative to the pelvis in the sagittal, frontal and transverse planes during gait with and without load in NCLBP.Core stabilization exercise therapy increases the between-trial variability and peak displacement of the lumbar relative to the pelvis in the sagittal, frontal and transverse planes during gait with and without load in NCLBP.

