### Participants

As there is no previous work to estimate the effect size for the kinematic variables considered here, we will conduct a pilot study to compute and estimate the effect size. Then, using power analysis, the required sample size with a power of 0.8 and an α of 0.05 will be determined. Assuming a large effect size, we anticipate recruiting 30 participants (15 in each group) for the study. Both males and females will be recruited in the study. The enrolment will be continued to reach the required sample size. Table 1 summarizes the inclusion and exclusion criteria for the CLBP group. Since the lumbar and trunk kinematics were not different during gait in the movement-based subgroups of NCLBP in a recent study [8], therefore in this study we will examined the NCLBP group regardless of their movement-based classification. Fifteen Healthy non-athlete subjects with no previous history of LBP will be included. Each healthy subject will be matched to a subject with LBP based on the age, sex, height, weight and BMI. In this group, subjects with a history of fracture, trauma and, pain of any other joints in the past also will be excluded from the study. In both groups participants will be excluded from the study if they have BMI higher than 30. Harsted et al. reported that CLBP with a BMI higher than 30 exhibited less variable and lower mean frontal plane range of motion compared to participants with a BMI below 30 [46]. However, less variability of movement of the trunk in this group is generally dependent to larger body mass instead of spine function [46].

**Table 1 Tab1:** Inclusion and exclusion criteria for the CLBP

Inclusion criteria	Exclusion criteria

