#### Statistical analysis

Data will be analyzed using SPSS version 21 (SPSS Inc., Chicago, IL) software. The normal distribution of data will be analyzed by a Kolmogorov-Smirnov Z test. If the distribution is normal, the outcomes of the studied measurements will be evaluated the absolute change from pre- to post- for VAS, ODI and the kinematic variables using a paired T-test in CLBP group. To determine homogeneity of variances (i.e., variances approximately equal across groups), Levene’s test will be employed. In addition, to evaluate the kinematics variables between CLBP and healthy group, an independent samples T-test will be used to reveal any difference between two groups. A non-parametric test will be used if the data are not normally distributed to compare across two groups (healthy and CLBP) using a Mann Whitney U exact test and, a Wilcoxon signed rank exact test will be used to compare of the variables in pre and post intervention in CLBP. A *p*-value of less than 0.05 will be considered statistically significant. According to the Raymond et al. study [59] minimal change that can be considered with perceived pain questionnaire and ODI in low back pain are clinically useful for interpretation of results. Results of VAS and ODI will be compared with range of minimal important change (MIC) value for pain (15.0–20.0 points) and ODI (10.0–12.0 points) [59].

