Our study will has some limitations, the main limitation of this study is that young and middle-aged NCLBP participants will be included, thereby, the generalizability is limited. In addition, haven’t a control LBP group and the lack of follow-up measurements after the postintervention measurements are other limitations in our study.

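### The programme's effectiveness is claimed from an uncontrolled pre-post test in patients, with data collected by the unblinded treating therapist

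*Protocol article*

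**What the plan says.** **The claim.** The abstract of the protocol article announces: "We will quantify the effectiveness of CSTP on the kinematic of trunk, lumbar and pelvis during gait". The hypotheses at the end of the Background are causal, for example: "Core stabilization exercise therapy increases the between-trial variability and peak displacement of the trunk relative to the pelvis". The Conclusion again says that the result will show the programme's effect on the kinematic measures.

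**The test.** Only participants with back pain are trained. Under Statistical analysis, pre-post change in VAS, ODI and kinematics is tested within that group: "the kinematic variables using a paired T-test in CLBP group", or a Wilcoxon signed rank test if the data are not normal. Healthy and back-pain groups are compared by an independent-samples t-test or a Mann-Whitney test, with no time point given. The VAS and ODI results are then set against minimal important change values of 15 to 20 and 10 to 12 points.

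**The comparator.** The limitations paragraph of the Discussion states that the study does not have "a control LBP group and the lack of follow-up measurements after the postintervention measurements are other limitations in our study".

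**The assessor.** The Examiner section says that "the same physiotherapist collect the pre-treatment and post-treatment data from each participant and also will provide core stabilization program". By the Recruitment and Informed consent sections, the same therapist also recruits and takes consent. The limitations paragraph does not mention this.

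**The healthy schedule.** The section on three dimensional motion analyses says "A three dimensional approach will be used to kinematic analysis of trunk, lumbar and pelvis pre/post treatment in all participants". The Methods part of the abstract mentions before-and-after evaluation only for patients.

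**The concern.** A paired test in one treated group asks whether the mean changed between two sessions. It does not ask why. Familiarity with the laboratory, a systematic difference in marker placement or reference posture, the natural course of back pain and regression to the mean all enter the same mean change as the training does. The person who delivers the training and knows the session also gathers the data at both sessions.

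As planned, a significant paired result would be reported as effectiveness, and a VAS or ODI change beyond the minimal important change could be read as a benefit of the programme. The design supports neither reading. Conceding that there is no control group does not repair this while the abstract, hypotheses and Conclusion keep the causal wording.

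**Working it through.** **Inputs from the article (Participants).** The plan says that "the required sample size with a power of 0.8 and an α of 0.05 will be determined", and: "Assuming a large effect size, we anticipate recruiting 30 participants (15 in each group) for the study". It gives no number for a large effect and no sidedness. I assume a standardised effect of 0.8 and a two-sided test.

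**Step 1: reproduce the 15.** For a paired t-test, power is the probability that a noncentral t variable with n − 1 degrees of freedom and noncentrality d√n exceeds the critical value.
- Paired, d = 0.8, power 0.80: n = 14.3, rounded up to 15. At n = 15 the noncentrality is 0.8 × √15 = 3.10 and power is 0.82.
- Two independent groups, d = 0.8: 26 per group by the exact t-test, or 25 by the normal approximation. One-sided, these are 21 and 20.

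Under these assumptions the planned 15 fits the within-patient pre-post test and no between-group test. The article leaves the final number to a pilot study.

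**Step 2: what a non-treatment shift does to that test.** Let the true treatment effect be zero and let other influences move the mean by s SD of change. The probability of significance is the same noncentral-t calculation with s in place of d, at n = 15 and two-sided 0.05. The values of s are assumed, because the article gives no retest data.

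| s (SD of change) | s√15 | P(significant) |
|---|---|---|
| 0 | 0 | 0.05 |
| 0.2 | 0.77 | 0.11 |
| 0.3 | 1.16 | 0.19 |
| 0.5 | 1.94 | 0.44 |
| 0.8 | 3.10 | 0.82 |

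The last row equals the power in Step 1: the test responds in the same way to a shift of a given size whatever its cause. Random marker re-placement error has s = 0 and only adds noise. Only a systematic difference between sessions moves the mean.

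**Step 3: what a comparison of change would offer.** With two independent groups the noncentrality is d√(n/2).
- At 15 per group and d = 0.8 SD of change: 0.8 × √7.5 = 2.19, power 0.56 (0.59 by the normal approximation).
- For 80% power: 26 per group.
- Smallest difference detectable with 80% power at 15 per group: 1.06 SD.

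This comparison keeps its 0.05 level only if the non-treatment shift is the same in both groups. Retest and measurement drift may be. Natural course and regression of back pain are not shared by people without back pain.

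**Step 4: the healthy schedule, side by side.**
- Three dimensional motion analyses: pre and post, all participants.
- The later statement on gait trials: recorded pre- and post-intervention, group not specified.
- Abstract, Methods: before and after, patients only.
- Statistical analysis: between-group test without a time point, and no test of change that involves healthy participants.

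These statements do not settle whether a second healthy session takes place or what it would be used for.

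**The case against.** The strongest reply is that a single treated group is a deliberate and disclosed choice, and that most outcomes are instrumented. Pain and disability are a VAS and a questionnaire. Angles come from motion-capture software, heel contact from a marker's lowest position, and the variability coefficients from published equations. The Kinematic analysis section separates pattern variability from offset variability because the former is less exposed to reference position. Comparing results with a minimal important change is ordinary practice.

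Much of this stands, and it rules out several stronger readings.

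- A reader might infer that the treating therapist scores the outcomes. The article says only that this person collects the data. Landmarks are palpated by a physical therapist, probably the same one. What remains is unblinded collection and possible influence on marker placement.
- A reader might infer that a second healthy measurement is taken and then ignored. That healthy participants return rests on a literal reading of one sentence, which the abstract does not support, and the undated between-group test could use post data. What is certain is that no planned test of change uses healthy data.
- A reader might want to express regression to the mean in VAS millimetres. The article gives no SD or retest correlation and sets no minimum pain score for entry, so no such figure can be drawn from it.
- The missing control group is not an undisclosed flaw.

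The reply does not meet the main point. Pattern variability lessens one source of session shift, but offset variability and peak displacement are also outcomes, and nothing in the plan addresses natural course or regression. The disclosure sits directly before a Conclusion that still promises to show the effect.

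**Conclusion.** The point holds as a mismatch between claim and design. The planned paired test can show change after the programme. It cannot attribute that change to the programme, and the unblinded assessment belongs among the limitations. For an assumed non-treatment shift of 0.2 to 0.5 SD of change, the chance of a significant result with no treatment effect is about 0.11 to 0.44 instead of 0.05, at n = 15 and two-sided. These are conditional illustrations and not estimates of the trial's actual error rate, because the documents do not show that a shift of any given size will occur.

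It would go too far to require the comparison of change with healthy participants as the primary test. At 15 per group its power is about 0.56 for an assumed 0.8 SD difference, and it cannot remove natural course or regression to the mean.

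**What to change.** 1. Restate the aims, hypotheses and conclusions as change after the programme, in place of its effectiveness or effect. Apply the same wording to the comparison of VAS and ODI with the minimal important change values.
2. Add to the limitations that the treating therapist, who is not blinded, collects the data at both sessions.
3. Have VAS and ODI completed by the participants themselves. Give the motion files codes, so that gait-event detection and the variability calculations are done without sight of group or session.
4. Reconcile the abstract, the section on three dimensional motion analyses and the Statistical analysis section on whether healthy participants are measured once or twice, and state the time point of the between-group test.
5. If they are measured twice, add patient change minus matched-control change as a supportive, not primary, kinematic analysis. State that it removes only shifts common to both groups, and that its power at 15 per group is about 0.56 for an assumed 0.8 SD difference.

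The cost is weaker claims and a little more analysis work. No extra visit is required, because item 5 applies only if the second healthy session is already planned.

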### Procedure

Before any intervention and after obtaining the informed consent form, baseline characteristic of participants (such as weight, height) will be measured, and then all of participants will be asked to take the warm up with 5 min of walking in the examination day. Examination will be performed in morning from 9 PM to 12 PM. The reflective markers are attached to the relative anatomic landmarks and participants will stand on the starting point then will performed free self-selected speed walking trials for 6 times, across a 10-m walkway. In order to avoiding the head rotation during walking, a visual target will set on the front of the walkway. A box with maximum 10% of body weight will anteriorly be used to load carrying trials [21]. The box is held with both hands while elbow flexed to 90 degrees, forearms are in mid pronation, wrists are in neutral and arms are beside the body. Participant will be instructed to walking with command, “START”. Then they walk so that they reach to the end point of walkway. Participants repeat each trials 3 times. After a few minutes rest, they started the trials with load.

### Program for core stability training

After the examination day, subjects with NCLBP will participate in the core stabilization program training. Initially, the anatomy and function of local back stabilizing muscles and the way they could be activated will be taught to the subjects. Training sessions will be performed on Saturday, Monday and Wednesday. In the beginning, each participant will perform a warm-up period consisted of stationary bicycle and stretching exercise for 10–15 min. These warm up program include: long sitting position and forward lining to the foot in order to stretching of the hamstring and gastrosoleus muscle, single and double knee to chest from supine position, spinal flexion-extension from 4-point kneeling position, side bending in standing position with and without contralateral arm elevation, Hip flexors stretch from the Thomas test position. According to the previous recommendations, a staged approach will be administered to the stabilization exercise program [53]. This program is designed over 16 individual sessions during 6 weeks. The exercises based on isometric activation of low back, abdominal and pelvis muscles and will be initiated with learning of abdominals, pelvic floor, diaphragm and multifidus muscles to contract isometrically in low load and repetition until their capacity to control the pelvic and lumbar movement are improved. Then the subjects will be learned abdominal hollowing/bracing (co-contraction) in a variety of postures and functional tasks: sitting, quadruped, standing, supine, kneeling, and prone, as well as different degrees of inclination to control loading/gravity. To ensure correct activation of the transversus abdominis muscle, it will be emphasized to the participants that the lower part of the anterior abdominal wall below the umbilical level would be needed to be “drawn in” with the action of this muscle. Also, bulging of the multifidus muscle will be needed to be felt under the therapist’s fingers when they will be placed on either side of the spinous processes of lumbar vertebrae, directly over the belly of this muscle [54]. Progressively participants will instruct to increase holding time and repetition of contraction up to 10 contraction repetitions × 10-s duration [53]. In the first session, the therapist will clearly instruct the patient on how to preferentially activate these muscles lasting about 30 to 45 min. In order to instruct the patient to contract the multifidus during exercise, physiotherapist will provide his fingers on the spinous process of L_4_-L_5_ directly over the muscle belly to felt bulging of the muscle. All training sessions will take place in the same location.

### Outcome measures

#### Pain and disability

Pain intensity will be assessed using a 0–100 visual analog scale (VAS), with 0 representing no pain and 100 representing the worst imaginable pain. Functional disability will be assessed by a Persian version of Oswestry Disability Index (ODI). The development of the ODI was initiated by John O’Brien in 1976 [55]. An ODI can be scored from the eight sections. For each section of six statements the total score is 5 [55]. Validity and reliability of the persian translated version of the ODI has been evaluated by Mousavi et al. and Baradaran et al. [56, 57]. ICC for individual items ranged from 0.43 to 0.80 [56] and 0.91 [57]. The Cronbach-alpha for the ODI was 0.69 [56] and 0.75 [57] showing good internal consistency in both studies.

